## Abstract

**Background:**

In early childhood allergy prevention (ECAP), parents act on behalf of their children. Parental health literacy and the availability of high-quality information, both online and offline, are crucial for effective ECAP. Recent research highlights three main points. First, parents need sufficient health literacy to discriminate between high-quality and low-quality information. Second, ECAP information behaviors may vary between phases of childhood development and according to individual circumstances. Third, to strengthen user-centeredness of available services, a better overview of parents’ information practices and needs and how they handle uncertainties is required.

**Objective:**

This study aims to explore why, how, and when parents search for and apply ECAP-specific health information and which individual (eg, understanding of advice) and organizational challenges (eg, information services, information complexity, and changing recommendations) they perceive and how they handle them. This study also aims to assess the needs and preferences that parents express for future information formats and contents. The findings should inform the practical design of ECAP information as well as formats and channels specific to different parent groups.

**Methods:**

The above-named issues will be explored with parents in four German cities as one element in our efforts to cover the spectrum of perspectives. Based on a mixed methods design, including qualitative and quantitative assessments, the first year serves to prepare focus groups, a piloted focus group guide, a short standardized survey adapted from the European Health Literacy Project, recruitment channels, and the recruitment of participants. After conducting 20 focus groups in the second year, data will be analyzed via a constant comparison method in the third year. Based on this, practice implications on channels (ie, Where?), formats (ie, How?), and contents (ie, What?) of ECAP-specific information will be derived and discussed with parents and associated project partners before its dissemination to relevant ECAP actors (eg, childcare institutions and pediatricians).

**Results:**

The study began with preselection of recruitment channels, drafting of recruitment and study information for potential participants, and agreement on a first full version of the guideline. Then, a detailed contact list was compiled of health professionals, administrative and social institutions, and relevant social media channels (N=386) to be approached for assistance in contacting parents. The recruitment was postponed due to COVID-19 and will start in January 2021.

**Conclusions:**

ECAP is a relevant example for assessing how users (ie, parents) handle not only health information but the various and continuous changes, uncertainties, and controversies attached to it. So far, it is unclear how parents implement the respective scientific recommendations and expert advice, which is why this study aims to inform those who communicate with parents about ECAP information.

**International Registered Report Identifier (IRRID):**

PRR1-10.2196/25474

## Introduction

### Background

#### Overview

The overall prevalence of children with allergies or asthma remains high and is often considered to be rising, despite the fact that exact numbers vary between regions [1-4]. While research on, and responses to, allergic diseases retain their traditional focus on treatment, nowadays prevention, immune system stimulation, and tolerance induction are considered increasingly important [5]. Hence, infants and young children may be a particularly important focus for prevention, because a person’s immune response to allergic triggers is formed early on in life [6]. For parents, this means that their role and the situation they find themselves in regarding early childhood allergy prevention (ECAP) has changed, particularly as new knowledge evolves continuously and often contradicts previous assumptions (eg, the effectiveness of deliberately exposing children to allergens, such as peanuts or eggs). This demands a more active, yet often less certain, parental role. Because of this and because recommendations given to parents change continuously [7-9], ECAP is a relevant example of how subject-specific health information is applied in daily (ie, regular) activities from four different perspectives, each with their own challenge.

#### Challenge 1: Information-Seeking Reasons and Motivations

Firstly, parents may search for information for different reasons and with varying motivations and individual circumstances [10]. Some may be concerned because of a known familial predisposition, some may have no particular risk but have more general concerns, while others may not have any specific interest. Apart from a particular risk status that triggers interest, different parental motivations may be evident at different stages of early childhood development. Also, a considerable proportion of parents may not seek ECAP-related information at all.

#### Challenge 2: Information Preferences

Secondly, evidence about parental information-seeking behavior and preferences regarding content, format, and delivery of information is crucial to adapt available services to parents’ specific requirements [11,12]. While there is ample evidence that many individuals lack health literacy—the ability to access, understand, appraise, and apply health information [13-15]—information regarding parents’ needs and preferences for ECAP-specific health information is scarce [16,17]. Research on needs and preferences relating to other topics suggests that available information is not tailored to target groups or according to the respective subjects [18]. It is also assumed that search behavior and preferences vary across different subjects and that parents are selective in seeking information (eg, during their children’s different developmental stages) [19].

#### Challenge 3: Information Formats

Thirdly, ECAP behavior and preferences may be influenced by available information formats. While the usage of online health information is increasing, the quality, safety, and reliability of available sources has been criticized in the past [20,21]. Further aspects, such as transparency, neutrality, appropriateness, and readability, may be equally important to ensure effectiveness [12,19,21,22]. This is also important because parents usually make use of more general information derived from public search engines rather than from specific sources for which a high degree of quality and a trustworthy evidence base can be assumed (ie, university- and health professional–authored sources) [12]. Another point of criticism of currently available online sources is that they are frequently overly technical, of limited accuracy, and contain too much information; in addition, there are no universal quality criteria for the development and provision of related services [18,23-28].

#### Challenge 4: Determinants of Information-Seeking Practices and Preferences

Lastly, parents’ information-seeking behavior and the respective stages and tasks related to searching, finding, appraising, and applying available information is influenced by their specific level of health literacy (see Methods section). For Germany, recent research highlights the prevalence of inadequate levels of health literacy in the population [13]. The association between health literacy and parents’ information and care practices has been discussed for other health issues (eg, obesity [29], food allergy [16], self-efficacy [30], weight control [31], and pediatric emergency utilization [32]). All studies highlight the negative effects of poor health literacy on parents’ health behavior; these studies suggest adjusting information sources and health care practices to health literacy levels [29] and developing strategies to support parents [30,33]. To develop respective materials and strategies, a better understanding of parents’ actual behavior and preferences is necessary [31]. In addition to the potential influence of health literacy, sociocultural habits, traditional beliefs, language barriers, past experiences, and routines regarding information use and access have been repeatedly described in the literature as important influencing factors. However, these aspects have not yet been assessed in the context of ECAP [34-37].

### Objectives

With the above-stated lack of empirical evidence on parental ECAP needs, preferences, and practices, the objectives of the planned study are shown in Table 1.

**Table 1 table1:** Objectives and themes of the study.

Objective	Theme
Assess reasons and motivations for searching for early childhood allergy prevention (ECAP) information among different parent groups, and assess how these reasons are further influenced by parents’ awareness of, trust and uncertainty with, and beliefs of risks and myths associated with allergy prevention	Reasons, motivations, awareness, and trust
Explore how parents search for and apply ECAP information and clarify the emphasis on digital vis-à-vis nondigital sources	Information behavior
Describe preferences for information formats	Information formats (ie, needs and preferences)
Describe parents’ health literacy and sociocultural backgrounds and whether these create differences for the use of ECAP information	Influencing factors
Explore how sociocultural backgrounds may influence the above described aspects (ie, relevance, awareness, needs, preferences, and information behavior)	Sociocultural determinants
Summarize and disseminate key points for health professionals regarding parental handling of, and preferences for, ECAP information	Implications for practice

## Methods

### Study Design

#### Theory and Framework

The study of health literacy has gained considerable momentum, both at national (ie, Germany) and international levels (eg, [38-42]), due to the many people who have difficulties with accessing, understanding, appraising, and applying health information [15,43]. In light of its growing importance, the National Alliance for Health Literacy published the German National Action Plan for Health Literacy in 2018 [14]; similar initiatives are in place internationally, for instance, in Scotland and the United States [44,45]. Since the aim is to assess parental handling of, and needs regarding, ECAP, health literacy is at the core of each aspect of this study. The framework summarizes health literacy as a construct, with determinants of functional, interactive, and critical health literacy on a continuum from the individual to the population level, with the latter often being criticized for receiving too little attention [46,47].

The framework (see Figure 1) will be applied to (1) the development of the focus group manual, (2) data analysis (ie, development of coding categories; see Data Analysis section), and (3) formulation of recommendations, regarding both future ECAP information design and potential adjustments of the health literacy model. This framework has been slightly adapted from the original version by Sørensen et al [46] to emphasize the relevance of population-level determinants and the social embeddedness of health literacy.

**Figure 1 figure1:**
[figure not shown]
Health literacy framework.

#### Study Population

##### Target Group

To gather insights about the range of potentially different parental ECAP information behaviors and preferences and to help develop tailor-made future information materials and communication channels, different groups of parents will be recruited: (1) risk-specific groups (ie, parents with or without a specific risk of their child developing an allergy, based on the parents having or not having a medically confirmed allergy) and (2) life stage–specific groups (ie, expectant, new, and experienced parents).

Overall, a self-developed sampling matrix will be employed for a better overview of the characteristics of recruited participants and to identify parental characteristics that are underrepresented in the overall sample. The matrix will account for the above-mentioned main identifiers—allergy risk and life stage—as well as further, more typical recruitment criteria, including age, gender, educational status, migration background, and familial status (ie, living with or without a partner). The respective information will be queried during the recruitment process using a short questionnaire.

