##### Recruitment Process

First, a list of contacts was compiled for health professionals (eg, pediatricians, gynecologists, and allergists) and for public and public health institutions (eg, kindergartens, family centers, and community offices) located in both urban and rural areas within a 10-km distance to the project sites in Germany (ie, Hanover, Magdeburg, Freiburg, and Regensburg) to reduce participants’ travel time. Respective contacts were searched for via (1) entries in medical online registers (ie, mainly online physician registries like Arztauskunft Niedersachsen), (2) coordinating bodies within public health (eg, the German Society for Allergy and Clinical Immunology, Landesamt für Gesundheit, and registries on insurance websites), and (3) general directories (eg, municipality websites, registries provided by municipalities for parents to find and choose a kindergarten or nursery, and local citizen administration and service offices). This will be complemented by (4) a Google search (eg, for further childcare institutions in specific cities) and (5) pre-established contacts (ie, mainly health professionals) from each project partner’s previous networks and collaborators of the project lead. From the overall list of contacts, those who can be expected to have the most direct and/or most frequent contact with the target group will be contacted first, such as kindergartens; we will contact further individuals and institutions if necessary. After completion of the search for recruitment agents, health professionals and institutions will be contacted personally to inquire about their support and availability for recruitment.

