## Discussion

A major step toward successful focus group conduct is the recruitment of a sample diverse in individual backgrounds and perspectives, for example, by including parents with and without allergic predispositions, expectant and more experienced parents, single parents, and those who are not native German speakers. Hence, it will be important to sensitize recruitment agents to this issue, to contact institutions supporting disadvantaged people, and to ask all participants to inform peers.

The inclusion of hard-to-reach groups (ie, those that do not receive the call for study participation, those who do not use the internet, those who do not have the time or resources for participation, those who feel uncomfortable participating in group discussions, those with low reading levels, and those who have difficulties reading German) could prove difficult. While this potential challenge cannot necessarily be circumvented completely, we will make sure to address individual actors and organizations with specific access to these groups, particularly family and childcare organizations with specific services (ie, *Familienhilfe*) and family centers located in social flashpoints. Also, recruitment could be done directly from low-education suburbs (eg, via distributing study flyers directly to each household). It will also be important to inform, for example, family centers’ staff early, discuss potentially necessary adaptations of the recruitment material (eg, language), and ask them to approach potential participants more directly (ie, in their role as a reference person for hard-to-reach groups).

Experiences from similar, yet unpublished, studies on parental health literacy conducted by the research team in Hanover will provide valuable help for structuring the discussions on ECAP, addressing issues that deserve particular attention (eg, reasons for not adhering to certain sources and revising or changing less relevant topics). The challenge here may be to go beyond a discussion of general information behaviors (eg, Googling) and trusted sources (eg, scientific experts), though not neglecting these issues, and instead emphasize issues such as trust, decision making, and health literacy skill development.

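### Allergy risk, one of two main identifiers, rests only on the parents' own confirmed allergy, so a non-allergic parent of an allergic child is classed as without risk

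*Protocol article*

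**What the plan says.** The Target Group section names two kinds of group. The risk-specific groups are "parents with or without a specific risk of their child developing an allergy", and the rule that assigns a parent to one side or the other is "based on the parents having or not having a medically confirmed allergy". The life stage–specific groups are "expectant, new, and experienced parents". On the sampling matrix the section says: "The matrix will account for the above-mentioned main identifiers—allergy risk and life stage". The further criteria it lists are "including age, gender, educational status, migration background, and familial status (ie, living with or without a partner"). A short recruitment questionnaire will collect this information; its items are not shown.

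Elsewhere the article describes risk more loosely. Challenge 1 of the Introduction says "Some may be concerned because of a known familial predisposition", and the Discussion aims for diversity "by including parents with and without allergic predispositions".

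The grouping is then used throughout. It structures the focus groups (Qualitative Data Collection), guides which groups are coded first and how groups are compared (Parent Focus Groups), and is among the parent groupings for comparing mean health literacy (Health Literacy Survey).

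**The concern.** The label is about the child, but the rule looks only at the parents' own diagnosis. An allergy in an older child is also family information about allergy, and a parent living with it may have strong reasons of their own to look for prevention information. The rule nevertheless puts that parent, if not allergic, with parents who have no such reason.

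For a parent whose only child already has an allergy, neither label fits well, because both concern an allergy that has yet to develop.

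The partner is a second gap. The rule speaks of the parents in the plural, but individuals are recruited, and it does not say whether the allergy of a partner who is not present counts.

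At stake is the first objective in Table 1, on reasons and motivations for searching among different parent groups, and the later advice on which parents need which information. If the without-risk groups contain parents with a direct allergy reason, the two sides will look more alike than they should, or a theme will be credited to the wrong group.

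**Working it through.** The article states no figure that depends on this rule, so there is none to reproduce. The check is mainly of the text.

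**1. Is the rule closed?** The Target Group section gives parental confirmed allergy as the sole basis. No other section adds an allergic child or sibling as a criterion. The matrix variables named do not include it. The list of further criteria is open-ended, so the questionnaire might record a child's allergy, but the printed risk rule would still not use it.

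**2. Can the affected parents enter?** Yes. New and experienced parents are targeted, and no exclusion is stated for families with an allergic child. For recruitment "a list of contacts was compiled for health professionals (eg, pediatricians, gynecologists, and allergists"), and Recruitment Channels plans an approach in physician practices. These routes plausibly reach parents whose child already has an allergy.

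**3. Which cases does the rule handle?**

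| Attending parent allergic | Partner allergic | Existing child allergic | Class under the printed rule |
|---|---|---|---|
| Yes | Any | Any | With risk, unless both parents must be allergic |
| No | Yes | Any | Not settled by the wording |
| No | No | Yes | Without risk |
| No | No | No | Without risk |

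The third row holds under every reading of the rule. The second depends on what the plural is taken to mean.

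**4. How many parents?** The article gives no share. For context, 20 groups × 6 participants = 120, which agrees with the approximate total in Quantitative Data Collection. The two illustrations below rest on assumptions that are not in the article.

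- *Allergic child (third row).* Assume that half the sample, 60 parents, is classed as without risk and that 5% to 20% of them have an allergic child. Then 60 × 0.05 = 3 to 60 × 0.20 = 12 parents are affected. Spread over 60 / 6 = 10 groups, that is 0.3 to 1.2 per group of 6.
- *Allergic partner (second row), only if the attending parent's status alone is used.* Let p be the share of parents with a confirmed allergy, and assume that partners are independent. By own status, p are at risk; by either parent, 1 − (1 − p)². With p = 0.20 this is 1 − 0.80² = 0.36, and with p = 0.30 it is 1 − 0.70² = 0.51. Among those classed as without risk by own status, the share with an allergic partner is p(1 − p)/(1 − p) = p, which is 6 × 0.20 = 1.2 to 6 × 0.30 = 1.8 per group of 6. If either parent's allergy already counts, this component is zero.

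**The case against.** A parent's confirmed allergy is a reasonable and checkable way to make familial predisposition operational, and a narrower working rule is not a contradiction. A reader might infer that Challenge 1 defines risk and that the Target Group section breaks the definition. It does not: Challenge 1 offers predisposition as one example of why some parents are concerned. What stands is that the rule captures only part of what the label is meant to describe.

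A reader might also infer that the life-stage contrast is distorted, because only families with children can have an allergic child. The article does not support this. A wrong risk label leaves the parent correctly labelled as new or experienced, and having an allergic child is a real feature of that stage. Only a comparison crossing risk with life stage would be affected, and none is stated.

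The partner calculation should not be read as the size of the problem. It covers one reading of an ambiguous phrase and says nothing about allergic children.

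The study is also qualitative. Codes are added inductively, so an account of an allergic child can be coded whatever the group, and adaptations are planned after the first four to five groups. The mean health literacy comparison sits within a descriptive analysis. This limits the harm but does not remove it: results are summarized by group, and what participants say depends on who else is in the discussion. That parents of allergic children are more motivated is a reasonable inference; the article does not document it.

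Finally, the questionnaire and the figure of project phases are not shown, so more may be recorded than is printed. The objection here is to the printed rule.

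**Conclusion.** The point holds as a weakness in a stated definition that should be corrected. Under any reading, a non-allergic parent of an allergic child can be placed in the without-risk group if the partner is not allergic either, and the treatment of an absent partner's allergy is unsettled. Risk is one of two main identifiers, alongside life stage, and not the sole grouping variable.

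The size is unknown. The 0.3 to 1.2 parents per group of 6 rests wholly on the assumed 5% to 20% share and an even split of the sample. The consequence is a possibly blurred risk contrast in reasons, needs and information behavior. No error rate or power is involved, and the life-stage labels are not affected.

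**What to change.** Before recruitment starts, which the article dates to January 2021:

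1. State that a medically confirmed allergy in either biological parent counts as parental allergy, whether or not that parent attends. Keep medical confirmation as the criterion.
2. Add two questions to the planned recruitment questionnaire: allergy in the other parent, and allergy in any existing child.
3. Do not place parents with an allergic child in the without-risk groups.
4. Keep these parents as an identifiable subgroup in the coding and comparison. Simply merging them with parents at risk by predisposition would mix experience of living with a child's allergy with anticipation of one.

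The cost is two short questions and a somewhat smaller pool of strictly without-risk parents. Changing the rule later is only a partial repair: transcripts can be relabelled, but the composition of a discussion already held cannot be changed.
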